#### Process and impact evaluation

Online survey data will be downloaded by MOVE staff from the online survey database and entered into an Excel spreadsheet. Responses will be grouped by MCHN nurse team and separated into trial arms. Responses will be counted and proportions of responses for each questions calculated. These data will be compared across trial arm and analyzed using bivariate chi-square tests of independence or other non-parametric analytical approaches where appropriate.

Qualitative data (interviews with key stakeholders) will be transcribed verbatim, coded thematically exploring NPT constructs and for any other significant patterns and any outliers.

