**Methods/design:**

MOVE is a cluster randomised trial of a good practice model of MCHN IPV screening involving eight maternal and child health nurse teams in Melbourne, Victoria. Normalisation Process Theory (NPT) was incorporated into the design, implementation and evaluation of the MOVE trial to enhance and evaluate sustainability. Using NPT, the development stage combined participatory action research with intervention nurse teams and a systematic review of nurse IPV studies to develop an intervention model incorporating consensus guidelines, clinical pathway and strategies for individual nurses, their teams and family violence services. Following twelve months’ implementation, primary outcomes assessed include IPV inquiry, IPV disclosure by women and referral using data from MCHN routine data collection and a survey to all women giving birth in the previous eight months. IPV will be measured using the Composite Abuse Scale. Process and impact evaluation data (online surveys and key stakeholders interviews) will highlight NPT concepts to enhance sustainability of IPV identification and referral. Data will be collected again in two years.

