#### *Impact evaluation* - o*nline survey data*

Three months after the end of the intervention, a second anonymous online survey of MCH nurses in both arms of the study (~160) was developed to assess their levels of confidence about and attitudes to IPV screening, perceived rates of inquiry about women’s and children’s safety, referral to family violence agencies for all family members, team functioning and support for IPV screening and perceptions of their own safety. The surveys and interviews will be repeated two years after the end of the intervention to assess sustainability of the screening processes. Interviews conducted by external staff with key stakeholders will also be conducted at the end of the intervention and two years later.

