### Data analysis and reporting

#### Women’s survey

The MCH consumer survey data will be cleaned, double-coded and entered into a secure database by an external company blinded to the study arms. It will then be forwarded to a statistician blinded to study arm. Women’s characteristics for socio-demographic and birth characteristics will be compared by trial arm to ensure that randomization was effective. The representativeness of the women responding to the survey (i.e. sample bias due to differential study participation rates) will be assessed by comparison with routine perinatal data for all women giving birth in the region for the comparison year (Victorian Perinatal Data Collection Unit, DHS).

All data will be analyzed by intention-to-treat and variance estimates in models will be adjusted for the effect of the clustered (LGA) selection of participants. We will analyze data using contingency table analyses for bivariate and binary logistic regression with robust standard errors for multivariate models. For primary outcomes, we will analyze data stratified by and adjusted for women’s abuse status and for potentially significant confounding variables (where randomization is less effective in removing bias across study groups), including women’s socio-economic status.

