### Two year follow-up

We propose to seek permission to obtain routine data for screening inquiry, safety plans and referrals for IPV two years after the MOVE implementation completion. We will also aim to conduct a survey with all nurses in the two arms of the MOVE trial to investigate the sustainability of the screening intervention, using NPT constructs. Analyses of these data will be conducted as outlined above.

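### Nurse-survey comparisons between arms, including the two-year repeat, are planned with a chi-square test that ignores the eight randomised teams

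*Protocol article*

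**What the plan says.** The abstract describes "a cluster randomised trial of a good practice model of MCHN IPV screening involving eight maternal and child health nurse teams". Four of the eight teams form the intervention arm (Intervention development phase), and the teams were stratified by births and paired in size (Randomization).

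Nurses are surveyed online six months into implementation (Data collection) and again three months after it ends. The later survey is "a second anonymous online survey of MCH nurses in both arms of the study (~160" nurses, and it covers confidence, attitudes, perceived inquiry rates, team functioning and team support. The section on impact evaluation adds: "The surveys and interviews will be repeated two years after the end of the intervention to assess sustainability of the screening processes".

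The analysis is given under Process and impact evaluation. "Responses will be grouped by MCHN nurse team and separated into trial arms", and proportions are calculated for each question. Then: "These data will be compared across trial arm and analyzed using bivariate chi-square tests of independence", with other non-parametric methods allowed where suitable. For the two-year data, the section Two year follow-up says only: "Analyses of these data will be conducted as outlined above".

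Clustering is addressed elsewhere. The survey sample size calculation uses an ICC of 0.02. Under Women's survey, the variance estimates of models are adjusted for local government area, and logistic regression with robust standard errors is specified. The same paragraph also says: "We will analyze data using contingency table analyses for bivariate".

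**The concern.** A chi-square test of independence takes its standard error from the number of individual respondents. Here the allocated unit is the team. Nurses in one team work under the same leader in the same council, and some survey items (team functioning, team support) describe the team itself. If answers within a team are positively correlated, the Pearson test understates the variance of the arm difference and rejects too often.

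The cluster adjustment in the protocol does not reach these data. It sits under the women's survey and is limited to variance estimates in models. Even if its opening reference to all data is read broadly, a bivariate chi-square is not such a model.

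At stake are claims that the model changed nurses' confidence, attitudes or team support, and that any such difference lasted two years. Each question is to be compared, so some spurious arm differences should be expected. The findings are intended for policymakers.

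**Working it through.** The protocol gives no error rate or sample-size calculation for the nurse surveys, so there is no figure of its own to reproduce.

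**Inputs**
- Teams: 8, 4 per arm (protocol).
- Nurses: about 160 (protocol), so 160/8 = 20 per team if all respond. The response rate is not stated; 60% response (12 per team) is an assumed alternative.
- ICC: 0.02 is the only value in the protocol and belongs to the women's survey. 0.05 and 0.10 are assumed.
- Level: two-sided 5% (assumed; not stated).
- Equal team sizes (assumed), and pairing ignored.

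**Formulas**
- Design effect: D = 1 + (m − 1) × ICC, with m responders per team.
- True type I error of the unadjusted test: 2 × [1 − Φ(1.96/√D)].

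Example: m = 20 and ICC 0.02 give D = 1 + 19 × 0.02 = 1.38. Then 1.96/√1.38 = 1.668, and the type I error is 9.5%.

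The formula was checked by beta-binomial simulation (200,000 runs per setting; true proportions 0.3, 0.5 and 0.7).

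| Per team | ICC | D | Formula | Simulated Pearson |
|---|---|---|---|---|
| 20 | 0.02 | 1.38 | 9.5% | 9.3-9.9% |
| 20 | 0.05 | 1.95 | 16.0% | 15.9-16.6% |
| 20 | 0.10 | 2.90 | 25.0% | 24.9-25.8% |
| 12 | 0.02 | 1.22 | 7.6% | 7.8-7.9% |
| 12 | 0.05 | 1.55 | 11.5% | 11.9-12.1% |
| 12 | 0.10 | 2.10 | 17.6% | 18.2-18.3% |

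**Sensitivity**
- Unequal teams (8 to 32 nurses): 10.1%, 18.0% and 28.1% at ICC 0.02, 0.05 and 0.10.
- Yates correction: about 7%, 13% and 21-22% with 20 per team; about 5%, 8% and 14% with 12 per team.

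**After the fix.** A t-test on the eight team proportions (6 df) gave a simulated type I error of 5.1-5.4% with equal teams and 4.8-5.2% with unequal teams.

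**Women's survey, only if its tables are unadjusted.** The protocol expects 55-65% of 5000 per arm to respond. At 55%, 5000 × 0.55/4 = 687.5 per team; at 65%, 812.5.
- Whole-sample items at ICC 0.02: D = 1 + 686.5 × 0.02 = 14.73 and 1 + 811.5 × 0.02 = 17.23. Type I error is about 61% and 64%.
- Items limited to women reporting IPV, at the protocol's 8-10% prevalence and the same ICC: 687.5 × 0.08 = 55 to 812.5 × 0.10 = 81.25 per team. D = 2.08 to 2.605, and type I error is about 17% to 22%.

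**The case against.** Several points on the other side deserve weight.

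- **Size.** A reader might infer that the false-positive rate simply is 10-25%. The protocol does not support that. The range needs full response and a nurse ICC of about 0.02 to 0.10, and no nurse ICC is given. At 0.02 with 60% response it is 7.6%, and a Yates-corrected test would then be close to nominal. Size-pairing might also lower the rates somewhat. This stands, so the magnitude must be stated conditionally.
- **Cause of correlation.** It is tempting to say that all eight teams share mentors and liaison workers. Both are described only as parts of the intervention model, and one liaison worker serves three of the four intervention teams. The argument for correlation across both arms has to rest on shared leadership, setting and team-level items.
- **Sustainability.** A reader might infer that the sustainability conclusions rest entirely on these tests. They also draw on two-year routine data and on stakeholder interviews.
- **Women's survey.** A reader might infer that its primary results are invalid. The protocol specifies cluster-robust logistic models, and that its bivariate tables are unadjusted is inferred from one compressed sentence in an article. This part can only be conditional and secondary.
- **Open wording.** The clause on other non-parametric approaches could accommodate a team-level test. It does not commit to one, and the test it does name is the wrong one.

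What survives is the central point: the protocol fixes a specific test that does not match the unit of randomisation. That differs from leaving detail to an analysis plan.

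**Conclusion.** The point holds for the nurse surveys, including the two-year repeat. For those, the only analysis outlined earlier is the chi-square comparison; how the two-year routine data will be analysed is less clear and is not part of this point.

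On the assumptions listed in the working, the Pearson test's error rate is about 8-10% at an ICC of 0.02 and about 18-25% at an assumed 0.10. The direction is secure for any positive within-team correlation; the size is not known from the protocol.

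These are process and impact comparisons. The nurse-reported elements of the primary outcomes are tied to routine data, and the logistic models for the women's survey are unaffected. The change should be made before analysis, but the point does not threaten the main trial result.

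**What to change.** In Process and impact evaluation, and by explicit reference in Two year follow-up, replace the plain chi-square with one of the following for all three nurse surveys:

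- a comparison of the eight team-level proportions, either by t-test on 6 df or by an analysis that keeps the size-pairing (four pairs, 3 df), with the choice stated in advance; or
- a cluster-adjusted chi-square (Donner or Rao-Scott type) with small-sample degrees of freedom.

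Under Women's survey, add a clause that any contingency-table test of an outcome by arm is also adjusted for clustering.

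No new data are needed, because nurse responses are already grouped by team. The price is lower power: with eight teams, fewer items will reach significance, and keeping the pairing costs further degrees of freedom. The precision given up was not real under within-team correlation.

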#### Randomization

The randomization of nurse teams at that time occurred at a public randomization meeting. Names of the MCHN teams, stratified by numbers of births per local government area and paired in size, were concealed in opaque envelopes and the random selection made by an invited guest from outside the project or research team. MCH Team Leaders were present to ensure the fairness of the process and to check the contents of the envelopes prior to their being sealed. For MOVE, all eight teams agreed to the reverse of the previous randomisation allocation, so that teams allocated to comparison status in MOSAIC formed the intervention arm for MOVE and those previously allocated intervention status formed the comparison arm.

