#### Intervention development phase – toward a model of sustainable good practice

This phase involved three strategies:

1.We conducted Participatory Action Research (PAR) with four volunteer MCHN consultants (one from each of four intervention MCHN teams) who explored the barriers and sought answers to these problems within their teams. PAR has been defined as ‘collective, self reflective inquiry that researchers and participants undertake, so they can understand and improve upon the practices in which they participate and the situations in which they find themselves’ [38]. Over a six-month period, at regular monthly meetings with MOVE staff, questions derived from earlier feedback in MOSAIC [26], discussion about barriers and enablers of IPV screening practices, and informed by the NPT framework [36] were agreed and nurse consultants took them away to their teams for discussion and feedback. The two groups (nurse consultants and MOVE staff) met over a six month period to discuss team feedback and reach agreement on the major aspects of a good practice model to be outlined in clinical pathways and guidelines. All meetings were recorded on tape and notes derived from them informed further discussion. We also drew on a GP systems intervention then being piloted in the UK (IRIS [23]) for strategies to strengthen links between clinicians and family violence services.

2. A systematic review of interventions (with controlled or comparison designs), guidelines or protocols targeted at improving the response of health care practitioners (HCPs) working with women experiencing IPV, their children and partners using abusive behaviors was conducted using Medline, Cochrane and Campbell Collaboration databases and CINAHL. Further details of the search terms and inclusion/exclusion criteria are available from the authors. Results were synthesized and presented to the nurse consultant and research group and the advisory group of key stakeholders.

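### The nurse online surveys are to be compared across arms with chi-square tests that treat about 160 nurses as independent, although eight whole teams were randomised

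*Protocol article*

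**What the plan says.** All references are to the protocol article.

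- **Unit of randomisation.** The Randomization section states: "The randomization of nurse teams at that time occurred at a public randomization meeting". The abstract describes a trial "involving eight maternal and child health nurse teams in Melbourne, Victoria", and the section on intervention development mentions nurse consultants, "one from each of four intervention MCHN teams". So there are four teams per arm.
- **Nurse surveys.** Nurses in both arms are surveyed online six months into implementation and, for the impact evaluation (about 160 nurses), three months after its end. A repeat is planned two years after the end. Besides confidence, attitudes and perceived inquiry, the impact survey covers "team functioning and support for IPV screening and perceptions of their own safety".
- **Test for these surveys.** Under Process and impact evaluation: "Responses will be grouped by MCHN nurse team and separated into trial arms". Counts and proportions follow, and then: "These data will be compared across trial arm and analyzed using bivariate chi-square tests of independence or other non-parametric analytical approaches where appropriate".
- **Clustering adjustment.** Under Women's survey: "variance estimates in models will be adjusted for the effect of the clustered (LGA) selection of participants".
- **Two-year nurse survey.** Under Two year follow-up: "Analyses of these data will be conducted as outlined above".

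**The concern.** A chi-square test of independence on pooled arms takes each nurse as a separate piece of evidence about the intervention. Allocation was by team, so differences between teams that have nothing to do with MOVE fall wholly on one arm or the other, and with four teams per arm they average out poorly. The test has no term for this variation.

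Some within-team correlation is likely on the document's own description. Each team has its own leader and local government employer, and some survey items ask about the team itself. Team is recorded and used to group responses, but it plays no part in the named test. The authors allow for clustering in the women's survey, both in the sample size and in the models, but say nothing of it for the nurses, who are the members of the randomised units.

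At stake is how the nurse-survey part of the impact evaluation is read, and the two-year nurse survey if the same method is carried forward. Arm differences in confidence, perceived inquiry or team support could be reported as effects of the model when they reflect ordinary differences between teams.

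**Working it through.** The document gives no power or error rate for the nurse surveys, so there is no stated figure to reproduce. The check is of the true error rate of the named test.

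**Inputs from the document.** Eight teams, four per arm; about 160 nurses, hence m = 160/8 = 20 per team; ICC 0.02, which was used for the women's survey sample size and is the only ICC given.

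**Assumptions.** Two-sided 5% level; nurse-level ICC between 0.02 and 0.10; full response with equal teams, then 60% response (m = 12) as a sensitivity case.

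**Step 1: design effect and true error.**

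DE = 1 + (m − 1) × ICC; true error = 2 × [1 − Φ(1.96/√DE)]

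| ICC | DE (m = 20) | 1.96/√DE | True error | Effective nurses (160/DE) |
|---|---|---|---|---|
| 0.02 | 1 + 19 × 0.02 = 1.38 | 1.67 | 9.5% | 116 |
| 0.05 | 1 + 19 × 0.05 = 1.95 | 1.40 | 16.0% | 82 |
| 0.10 | 1 + 19 × 0.10 = 2.90 | 1.15 | 25.0% | 55 |

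**Step 2: simulation with no intervention effect.** Beta-binomial data, 100,000 replicates, four against four teams. The m = 20 columns cover true proportions of 0.3, 0.5 and 0.7; the m = 12 column uses 0.5.

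| ICC | Pearson, m = 20 | With Yates correction, m = 20 | Pearson, m = 12 | t-test on team proportions, 6 df, m = 20 |
|---|---|---|---|---|
| 0 | 4.8-5.2% | 3.3% | not run | 5.1-5.2% |
| 0.02 | 9.3-9.8% | 7.0-7.1% | 8.1% | 5.1-5.2% |
| 0.05 | 15.8-16.5% | 12.7-12.9% | 12.2% | 5.0-5.2% |
| 0.10 | 25.0-25.8% | 21.4-21.6% | 18.4% | 5.1-5.3% |

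Unequal teams (10, 16, 24 and 30 nurses in each arm) give slightly higher Pearson rates: 10.1%, 17.3% and 27.4% at ICC 0.02, 0.05 and 0.10.

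**Step 3: what a valid test can detect.** For a 50% item, SE of the arm difference = √[2 × 0.25 × DE/(20 × 4)]. The difference detectable with 80% power on 6 df is about (2.447 + 0.906) × SE = 3.353 × SE.

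- ICC 0.02: SE = 0.0929, about 31 percentage points.
- ICC 0.05: SE = 0.1104, about 37 points.
- ICC 0.10: SE = 0.1346, about 45 points.

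**Step 4: does the adjustment elsewhere reach these data?** It stands under the women's survey heading and speaks of variance estimates in models. A bivariate chi-square test is not such a model, and the nurse surveys have their own heading with their own stated test. The adjustment does not reach them.

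**The case against.** **The size rests on assumptions.** A reader might infer that false arm differences will occur 16-25% of the time. The document does not support that as a fact. It needs a nurse-level ICC of 0.05-0.10, close to full response, a two-sided 5% level and no continuity correction, and none of these is stated. At ICC 0.02 with a Yates correction the rate is about 7%. This part of the objection stands, so the size must be given as a range with its conditions. It does not remove the defect, since any positive within-team correlation inflates the error of this test.

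**The tests carry limited weight.** A reader might also infer that the trial's main conclusions, or its whole case on sustainability, are at risk. They are not. The primary outcomes come from the women's survey and routine data. Stakeholder interviews also inform the impact evaluation, and routine data on inquiry, safety plans and referrals also inform sustainability and safety. This stands and limits the consequence to supporting evidence. Nor can one say how many spurious findings to expect, because the document gives neither the number of items nor a significance threshold.

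**The wording leaves room.** Responses are grouped by team, and other non-parametric approaches are allowed where appropriate; a team-level permutation or rank test would fit that wording. This is partial mitigation only. Clustering is not mentioned, and the test that is named ignores it.

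**Correlation within teams is not shown.** The answers are individual perceptions, and one liaison worker served three teams, so that exposure is not specific to a team. It is fair that no passage supports a very high ICC. Separate leaders and employers and team-level items still make zero correlation an unsafe assumption.

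**Conclusion.** The point holds in limited form. The protocol names a test for the nurse surveys that does not match the unit of randomisation, and the clustering adjustment given elsewhere does not cover it. Because the test is stated, this is more than a detail left to an analysis plan.

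With about 20 respondents per team and a two-sided 5% level, the true error is about 10% at ICC 0.02, a value given for women and only borrowed here. It is 16-25% at an assumed nurse-level ICC of 0.05-0.10. At 60% response the simulated range over the same ICCs is about 8-18%. With a continuity correction and full response it is about 7-22%.

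The consequence is confined to the nurse-survey comparisons in the process and impact evaluation and, through the cross-reference, the two-year nurse survey. No primary outcome depends on it. It should be corrected because the correction is simple and the results are meant to inform policy.

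**What to change.** Under Process and impact evaluation, replace the individual-level test with one of the following, and show the eight team values for every item.

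1. **Team-level comparison.** Compute the proportion or mean score in each team and compare four with four by a t-test on 6 df or a permutation test. State whether the pairing of teams by size described under Randomization is used, because it changes the test. Unpaired permutation has 70 allocations (8 choose 4), so the smallest two-sided p-value is 2/70 = 0.029. With four pairs there are 2⁴ = 16 allocations and the smallest is 2/16 = 0.125, so a paired permutation test could never reach 5%. A paired t-test would have 3 df.
2. **Model.** Use team as a random effect, with a small-sample correction to the degrees of freedom.
3. **Description only.** Report the items by team and arm without p-values. This is reasonable given the power in Step 3 of the working.

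Apply the same rule to the two-year nurse survey by an explicit statement there.

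**Cost.** A sentence or two of analysis wording and no new data, since responses are already grouped by team. The real price is wider intervals and low power: four against four teams can detect only large differences, about 31 percentage points for a 50% item at ICC 0.02 and more at higher ICCs.
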